## Abstract

**Background:**

Local anesthetics (LAs) are regularly used to alleviate pain during medical or surgical procedures. Their use is generally considered safe, but exceeding the maximum recommended doses can lead to LA systemic toxicity, a rare but potentially lethal complication. Determining maximum safe doses is therefore mandatory before performing local anesthesia, but rules are often unclear and the factors affecting dose calculation are numerous. Mobile health apps have been shown to help clinical decision-making, but most currently available apps present significant limitations. The Local Anesthetics Dose Calculator (LoAD Calc) app was designed to overcome these limitations by taking all relevant parameters into account. Before deploying this app in a clinical setting, it should be tested to determine its effectiveness and whether clinicians would be willing to use it.

**Objective:**

The primary objective will be to evaluate the effectiveness of the LoAD Calc app through written simulated cases. The secondary objective will be to determine whether physicians find this app easier, faster, and safer than the methods they generally use.

**Methods:**

We describe a parallel-group randomized controlled trial protocol. Anesthesiologists working at the Geneva University Hospitals will be invited to participate. Participants will be asked to compute the maximum dose of LA in 10 simulated clinical cases using 3 different LAs. The maximum safe dose will be determined manually using the same calculation rules that were used to develop LoAD Calc, without using the app itself. An overdose will be considered any dose higher than the correct dose, rounded to the superior integer, while an underdose will be defined as the optimal calculated dose minus 20%, rounded to the inferior integer. Randomization will be stratified according to current position (resident vs registrar). The participants allocated to the LoAD Calc (experimental) group will use the LoAD Calc app to compute the maximum safe LA doses. Those allocated to the control group will be asked to use the method they generally use. The primary outcome will be the overall overdose rate. Secondary outcomes will include the overdose rate according to ideal and actual body weight and to each specific LA, the overall underdose rate, and the time taken to complete these calculations. The app’s usability will also be assessed.

**Results:**

A sample size of 46 participants will be needed to detect a difference of 10% with a power of 90%. Thus, a target of 50 participants was set to allow for attrition and exclusion criteria. We expect recruitment to begin during the winter of 2023, data analysis in the spring of 2024, and results by the end of 2024.

**Conclusions:**

This study should determine whether LoAD Calc, a mobile health app designed to compute maximum safe LA doses, is safer and more efficient than traditional LA calculation methods.

**International Registered Report Identifier (IRRID):**

PRR1-10.2196/53679

## Introduction

### Background

Local anesthetics (LAs) are used daily by physicians to perform minor procedures. While the doses they use are generally limited, anesthesiologists often use higher doses to perform regional anesthesia techniques [1]. While the advantages of such techniques are undeniable, using high LA doses increases the risk of local anesthetic systemic toxicity (LAST), a potentially lethal complication associated with the use of these agents [2]. The actual incidence of LAST is unknown since most minor symptoms are not specific and because LAST awareness varies considerably between practitioners [3,4]. The incidence reported in scientific studies varies from 0.04 to 1.8 per 1000 regional anesthesia procedures but is probably underestimated [5,6]. The main risk factors seem to be inadvertent intravascular injections and inappropriately large doses [7,8].

Prevention of intravascular injection can be achieved by ultrasound guidance and careful aspiration during the procedure, while adequate calculation of the maximum dose of LA before administration is the best way to avoid incorrect doses.

Although different guidelines have been created to help clinicians calculate the maximum safe LA doses, quickly and reliably determining such doses often proves difficult in clinical practice [9]. Many anesthesiologists rely on mental calculation (with or without a pen and paper aid), and some use calculators. These methods are, however, often challenging and inaccurate, especially if LA mixtures are used or when patients present multiple comorbidities [10]. More advanced solutions have been developed to support LA dosage calculation, such as the nomogram created by Williams and Walker [11]. The main limitation of this solution is that the nomogram must always be at hand. Moreover, specificities such as ideal body weight (IBW) calculation and adaptation in the case of relevant comorbidities are indicated but not directly integrated into dose determination.

To facilitate the calculation of safe maximum LA doses, a mobile health (mHealth) app, Local Anesthetics Dose Calculator (LoAD Calc), was developed at the Geneva University Hospitals [12]. This app takes all relevant parameters (IBW and actual weight, height, age, medications, and comorbidities) into account and allows the use of a mixture of 2 different LAs. Since smartphones have widely replaced older paging systems and are therefore always at hand, this mHealth app could be an appropriate solution to enable anesthesiologists to efficiently compute safe maximum LA doses.

### Objectives

This study protocol follows the hypothesis that LoAD Calc, an mHealth app designed to help clinicians calculate maximum safe LA doses, is safer and more effective than traditional methods. Thus, the primary objective will be to evaluate the effectiveness of the LoAD Calc app by using it to compute the maximum single doses of LA in written simulated cases. The secondary objective will be to determine whether physicians find this app easier, faster, and safer than the methods they generally use.

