### Study Design

This will be a monocentric, parallel-group, randomized controlled trial based on clinical vignettes. The protocol was developed according to the Standard Protocol Items: Recommendations for Interventional Trials (SPIRIT) statement (Multimedia Appendix 1) [14]. Given its design, the investigators will not be blinded as to the intervention. Nevertheless, participants will not be informed that there are 2 different arms and will not be told the exact outcomes studied, even though they will be provided with general information regarding the study. In addition, the data analyst will be blinded as to participant allocation by renaming the groups before sending data for statistical analysis. Randomization will be stratified according to current position (resident vs registrar).

Results will be reported according to the CONSORT-EHEALTH (Consolidated Standards of Reporting Trials of Electronic and Mobile HEalth Applications and onLine TeleHealth) guidelines [15]. Relevant elements of the CHERRIES (Checklist for Reporting Results of Internet E-Surveys) will be included since web-based questionnaires will be used in the course of this study [16].

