### Inclusion and Exclusion Criteria

All resident physicians and registrars working in the HUG anesthesiology department will be eligible for inclusion. The only exclusion criteria will be current or previous use of the LoAD Calc app. This criterion will be assessed by a screening question asked after the completion of all study vignettes.

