**Page 3: demographics**
Gender (multiple-choice questions with only 1 acceptable answer)Age (free text with regular expression [regex] validation rule)Position (multiple-choice questions with only 1 acceptable answer; custom answer accepted)Years since graduation (free text with regular expression [regex] validation rule)Years of practice in anesthesiology (free text with regular expression [regex] validation rule)Specialist diplomas (custom answer accepted; multiple-answer question with more than 1 answer accepted)

After completing the vignettes, the participants allocated to the LoAD Calc group will be asked to complete the French version of the System Usability Scale [18], the translation of which has been validated [19]. Participants allocated to the control group will then be asked which methods they used to calculate LA doses.

Finally, both groups will have to answer a question based on a 10-point Likert scale to assess their confidence as to the method they used to carry out the maximum safe LA dose calculations, from score 1 (absolutely not confident) to score 10 (perfectly confident).

The whole study sequence is summarized in Figure 1.

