### Outcomes

The primary outcome will be the overall overdose rate, according to the method used. To assess this outcome, the maximum acceptable dose in milligrams, or milliliters, must therefore be established. While this might seem straightforward at first sight, it is actually rather complex. Indeed, although maximum safe doses are calculated in milligrams, anesthetists administer a volume of LA (the concentration of which can vary) rather than a quantity of LA. Therefore, even though toxicity is related to the quantity (in milligrams) of LA administered, it is clinically more relevant to determine the maximum volume (in milliliters) of LA that can be used for a particular patient. Consequently, after applying the rules described in Textbox 1, a quantity in milligrams will be obtained. It will then be converted in milliliters according to the concentration of the LA used in the vignette. This volume will then be rounded to the inferior integer. To be less conservative, 1 mm will be added to this calculated volume, and the total will represent the maximum acceptable volume. An overdose will be considered any dose higher than this maximum acceptable volume or than its corresponding LA quantity in milligrams.

The secondary outcomes will be the overall overdose rate, considering the simulated patient’s ideal weight and the simulated patient’s actual weight, the overdose rate according to each LA studied, and the overall underdose rate. An underdose will be defined as the maximum acceptable volume minus 20% (or its corresponding LA quantity in milligrams), rounded to the inferior integer. This is an empirical choice since anesthetic underdose can only be determined clinically [20,21].

Other secondary outcomes will be the time taken to complete these calculations, the app’s usability, and the physicians’ confidence in using the method they were allocated to. The app’s usability will be evaluated using the System Usability Scale [18]. Provided that the statistical assumptions are met, factors associated with a higher probability of overdose or underdose will also be assessed.

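### The secondary objective asks whether physicians find the app easier, faster and safer than usual methods, but ease is rated in the app arm only and perceived safety is reached only through a confidence item

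*Protocol article*

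**What the plan says.** The secondary objective, given in the Abstract and again under Objectives, reads: "The secondary objective will be to determine whether physicians find this app easier, faster, and safer than the methods they generally use".

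The design is described under Study Design: "This will be a monocentric, parallel-group, randomized controlled trial based on clinical vignettes". The same section says that "participants will not be informed that there are 2 different arms and will not be told the exact outcomes studied". Under Inclusion and Exclusion Criteria, "The only exclusion criteria will be current or previous use of the LoAD Calc app".

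The questions put after the vignettes are described in Consent and Study Sequence, below the first questionnaire:

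- App arm: "the participants allocated to the LoAD Calc group will be asked to complete the French version of the System Usability Scale".
- Control arm: "Participants allocated to the control group will then be asked which methods they used to calculate LA doses".
- Both arms: "both groups will have to answer a question based on a 10-point Likert scale to assess their confidence as to the method they used". The scale runs from 1 to 10.

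The Outcomes section makes the overall overdose rate the primary outcome. After the dose-related secondary outcomes it continues: "Other secondary outcomes will be the time taken to complete these calculations, the app’s usability, and the physicians’ confidence in using the method".

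**The concern.** The objective has two features that the outcomes must match. It is comparative (app against usual methods), and it concerns what physicians think, since it asks what they find. A measure that answers it has to be an opinion, and it has to be available for both methods.

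The usability scale is an opinion, but it is collected for one method only. Completion time and overdose rate are collected for both methods, but they are not opinions. Only the confidence item meets both conditions, and it asks about neither ease nor speed, and not directly about safety.

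What is at stake is how the result will be reported. A favourable usability score in the app arm, placed under a comparative objective, invites the statement that physicians found the app easier than what they normally do. The data described could not support that statement, because nobody in the control arm rates ease.

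**Working it through.** The point itself rests on no figure, so the main check sets each term of the objective beside the measures that the text describes.

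| Term | Measure described | App arm | Control arm | Compared as randomized? | Perception? |
|---|---|---|---|---|---|
| Easier | System Usability Scale | yes | no | no | yes, of the app only |
| Faster | Time to complete the calculations | yes | yes | yes | no, measured |
| Safer (actual) | Overdose rate (primary outcome) | yes | yes | yes | no, measured |
| Safer (perceived) | 1-10 confidence in the method used | yes | yes | yes | indirect |

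1. *Ease.* A between-arm difference needs a score in each arm. The control arm has none, so the difference is undefined and a larger sample would not help. A within-person comparison is also absent. App-arm participants have a usual method and could be asked to compare from memory, but no such question is described. Controls could not be asked, because users of the app are excluded.
2. *Speed.* Time is compared between arms. Perceived speed is not collected.
3. *Safety.* The overdose rate compares actual safety. The confidence item concerns the method used to work out the maximum safe dose, so it bears on perceived safety. It remains a proxy: a physician can be confident in a method that overdoses.

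A second check asks what a rating taken in both arms could show at the planned size.

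- Inputs, from the Results and Statistical Analysis sections: difference 10%, SD 10%, power 90%, two-sided alpha 0.05, 23 per arm, target 50 in total.
- The plan's own figure: d = 10/10 = 1.0. The normal approximation gives n per arm = 2 × (1.960 + 1.282)² / 1.0² = 21.01, rounded up to 22, or 44 in total. The two-sample t test gives 22.02, rounded up to 23, or 46 in total. The stated 46 is reproduced.
- For a new rating with 80% power and two-sided alpha 0.05, the detectable standardized difference by t test is 0.84 SD with 23 per arm and 0.81 SD with 25 per arm (50/2, assuming equal arms).

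A common ease rating would therefore detect a large difference only. It would still give an estimate with a confidence interval, which the current plan cannot.

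**The case against.** The strongest case on the other side has four parts.

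*Much of the objective is covered.* Completion time, overdose rate and confidence are all taken in both randomized arms, and the hypothesis under Objectives speaks of the app being safer and more effective, which the overdose rate tests directly. This stands. A reader might infer that the secondary objective cannot be answered at all. The documents do not support that: measured speed and actual safety are compared, and perceived safety has an indirect randomized measure.

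*A parallel-group design is no defect here.* A reader might also infer that the objective fails because nobody uses both methods. That does not follow. The same rating given in each arm is a valid contrast without within-person comparison, as the confidence item already shows. The gap is one missing control-arm measure, not the design.

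*A one-arm usability scale is defensible.* The outcome is named as the usability of the app, and the control condition is a mix of mental arithmetic, paper, calculators and other aids, for which a system-usability instrument may fit poorly. This stands as a reason to keep that scale in the app arm. It does not supply a comparator for ease, and a short generic rating would suit any method.

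*The article is condensed.* The post-vignette questions are summarised in prose, and the study-sequence figure is not available. A further item cannot be excluded. However, the text says explicitly which arm receives which questionnaire, and that stated allocation is what fails to match the stated objective.

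**Conclusion.** The point holds as a partial mismatch between objective and outcomes. Of the three terms, ease has no between-arm measure: none of about 25 controls supplies a rating. Perceived safety rests on a confidence proxy, and perceived speed is not collected. Measured speed and actual safety are properly compared as randomized.

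The primary outcome, its sample size and the main conclusion about overdose are unaffected. The consequence is confined to the secondary objective: followed as written, the plan gives no basis for saying that physicians found the app easier than their usual methods.

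This assumes that the post-vignette questions are those described in the text. The figure of about 25 controls assumes that the target of 50 is reached and divided equally.

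**What to change.** Preferred: after the vignettes, give both arms the same short rating of ease, and ideally of perceived speed and perceived safety, each worded for the method the participant has just used. Compare these between arms as randomized. Keep the System Usability Scale as a descriptive outcome in the app arm, and keep the confidence item as it is.

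Alternative without new data: reword the secondary objective to what is collected, namely time and confidence compared between arms and app usability described in one arm, and draw no conclusion that physicians found the app easier.

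If app-arm participants are also asked to compare the app directly with their usual method, label those answers as supportive and non-randomized. They rely on recall and are open to demand effects, particularly in the hospital that developed the app.

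Cost: a few web questions, an estimated two minutes in a session of at most one hour. The downside is a slightly longer session. Because the questions follow the vignettes, they cannot influence the dose answers. The Results section says that recruitment waits for acceptance of the protocol so that adjustments can be made, so the change can still be made before the first participant.

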## Methods

### Ethical Considerations

A synopsis of the study protocol was presented to the regional ethics committee (Commission Cantonale d’Ethique de la Recherche [CCER]). This committee confirmed that this project does not fall within the scope of the Swiss Federal Act on Research involving Human Beings and issued a “declaration of no objection” (CCER 2022-01577) [13]. This study protocol does not fall within the scope of the Swiss Federal Act on Research involving Human Beings [13]. It will nevertheless be presented to the regional ethics committee to ascertain that no important or relevant ethical consideration was omitted.

Participants will be told that participation is entirely voluntary, that there will be no consequence if they refuse to participate, and that they will be able to withdraw at any time without explanation. All participants will be asked to sign an electronic consent form immediately after logging in. There is no compensation for participation in the study.

### Study Design

This will be a monocentric, parallel-group, randomized controlled trial based on clinical vignettes. The protocol was developed according to the Standard Protocol Items: Recommendations for Interventional Trials (SPIRIT) statement (Multimedia Appendix 1) [14]. Given its design, the investigators will not be blinded as to the intervention. Nevertheless, participants will not be informed that there are 2 different arms and will not be told the exact outcomes studied, even though they will be provided with general information regarding the study. In addition, the data analyst will be blinded as to participant allocation by renaming the groups before sending data for statistical analysis. Randomization will be stratified according to current position (resident vs registrar).

Results will be reported according to the CONSORT-EHEALTH (Consolidated Standards of Reporting Trials of Electronic and Mobile HEalth Applications and onLine TeleHealth) guidelines [15]. Relevant elements of the CHERRIES (Checklist for Reporting Results of Internet E-Surveys) will be included since web-based questionnaires will be used in the course of this study [16].

### Clinical Vignettes

A total of 10 clinical vignettes will be developed for the purpose of this study. These vignettes will describe clinical cases requiring the use of LAs for regional anesthesia. We will include 3 of the most commonly used LAs in these vignettes: lidocaine, levobupivacaine, and ropivacaine. Some vignettes will ask the participant to use LA mixtures, and several will include comorbidities or medications requiring dose adaptations.

For each vignette, 3 authors will be required to determine the maximum dose of LA the simulated patient should receive according to the rules used to develop the LoAD Calc app [12], without using the app. These rules, which are derived from the scientific literature, are summarized in Textbox 1. They were reviewed and approved by clinical pharmacologists and toxicologists [12]. Any disagreement will prompt a review of the vignette. Final vignette approval will only be possible if a consensus can be reached.

Dosage elements and app rules used to calculate the maximum safe dose of local anesthetics, adapted from Suppan et al [12].
**Dose limit for a single LA (local anesthetic)**
Levobupivacaine: 2 mg/kg (maximum 150 mg/dose)Lidocaine: 3 mg/kg (maximum 300 mg/dose)Ropivacaine: 3 mg/kg (maximum 225 mg/dose)
**Influence of epinephrine on dose limit**
Levobupivacaine: 3 mg/kg (maximum 150 mg/dose)Lidocaine: 7 mg/kg (maximum 400 mg/dose)Ropivacaine: 3 mg/kg (maximum 225 mg/dose)
**Determination of calculation weight (CW)**
Calculation of BMICalculation of ideal body weight (IBW; Devine formula)Application of the following algorithm to define CW:weight≤70 kg and BMI<30 and IBW >weight → CW=weightweight≤70 kg and BMI<30 and IBW ≤weight → CW=IBWweight≤70 kg and BMI≥30 → CW=IBWweight>70 kg and IBW>70 → CW=70weight>70 kg and IBW≤70 → CW=IBW
**Dose adaptation depending on health conditions and drugs**
ConditionsOld age (70 years or older)Renal dysfunction (glomerular filtration rate [GFR]<50 mL/minute)Hepatic insufficiency (prothrombin time <50%)Heart failure (left ventricular ejection fraction≤30%)PregnancyDrugs decreasing LA metabolismList of drugs decreasing LA metabolismMajor CYP1A2 inhibitors: ciprofloxacin, norfloxacin, and fluvoxamineMajor CYP3A inhibitors: azole antifungals, macrolides, calcium channel blockers, HIV antiretroviral therapy, and tyrosine kinase inhibitorsIf 1 condition is present, the calculator reduces the total maximum dose by 20%If 2 or more conditions are present, the calculator reduces the total maximum dose by 30%.
